### Data collection

3.3

Participants will be asked to complete a series of web-based surveys at baseline, six weeks and 12 weeks. These surveys include validated scales and objective questions on COVID-19 infection and medical history. The validated questionnaires assess stress, mood states, resilience, and overall wellbeing. Questionnaires, weekly activity diaries, and medical history, will be collected using REDCap. All surveys will all be automated and the study team will have minimal interaction with the participants. All health information provided by the participants is self-reported.

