### Measures

3.4

Each participant will be asked to respond to 8 validated neuropsychological scales assessing stress (Perceived Stress Scale, PSS), anxiety and depression (PHQ-4), joy predisposition (DPES-Joy Subscale), mindfulness awareness (MAAS), resilience (BRS), mental well-being (WEMWBS), and post-traumatic growth (PTGI). PSS is defined as the primary outcome while BRS is the key secondary outcome.

**Questionnaires**. The following questionnaires are incorporated into the study survey and will be administered to the study participants:

*Perceived Stress Scale (PSS).* PSS is a 10-question validated instrument that assesses stress. Participants are asked to rate on a scale of 0 (never) to 4 (very often) how often they agree with various statements designed to assess the degree to which life situations are appraised as stressful. Items from each of the 10 questions are then summed to create a total perceived stress score.

*4 Item-Patient Health Questionnaire measuring Anxiety and Depression (PHQ-4).* Four questions rated on a scale of 0 (Not at all) to 3 (Nearly every day). The sum is computed for the responses and scores range from 0 to 12. Categories of psychological distress are classified as: None (0–2 score), Mild (3–5 score), Moderate (6–8 score) and severe (9–12 score). Anxiety subscale is calculated by measuring sum of item 1 and 2 (score range, 0–6; scores greater than 3 considered positive for anxiety screening.) Depression subscale is calculated by measuring sum of item 3 and 4 (score range, 0–6; scores greater than 3 considered positive for depression screening.)

*Dispositional Positive Emotion Scale- Joy Subscale (DPES-Joy).* The joy subscale of DPES is a 6-item questionnaire that measures a dispositional tendency to feel joy in life. Participants report their level of agreement to each item on a scale of 1 (Strongly agree) to 7 (Strongly disagree) and a mean score is calculated.

*Mindfulness Attention Awareness Scale (MAAS)- short form.* MAAS - short form is a 5-question validated instrument that assesses mindfulness and attention while performing routine activities of daily living. Participants are asked to rate on a scale of 1 (Almost Always) to 6 (Almost Never) the frequency of occurrence for each experience. A mean score is then computed using items from each of the 5 questions to calculate the individual's MAAS score.

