### Analysis

3.6

Baseline characteristics of participants will be recorded. Continuous data will be presented as means ± standard deviation or median (interquartile range) depending on the distribution of the data and assessed with a parametric paired *t*-test or non-parametric Wilcoxon signed rank test, as appropriate. Normality will be assessed with the Shapiro-Wilk test. Categorical data will be presented as frequencies and percentages and assessed with a chi-square or Fisher's exact test, as appropriate. All primary analyses will be assessed using intention-to-treat principles. SAS 9.4 (SAS Institute Inc., Cary, NC) will be used for all analyses with two-sided p-values < 0.05 considered statistically significant.

Aim 1 Analysis. To quantitatively assess the effects of Isha yoga practices between seasoned practitioners and the control groups on measures such as perceived stress, resilience, and overall wellbeing by use of validated scales at baseline, 6 weeks and 12 weeks. We have defined Perceived Stress Score as our primary outcome and Brief Resilience Scale scores as our key secondary outcome. Given the continuous nature of the scales used to assess stress, resilience and measures of well-being, differences between groups will be assessed with a parametric or non-parametric *t*-test. Multivariable regression may be utilized to adjust for potential confounders that deem to vary between the groups based on the univariable analysis prior to that. The distribution of the dependent variable will depend on the actual distribution of the scales recorded in the study. A mixed effect approach in modeling will address the similarity of the subjects enrolled in the study as friends or by matching, by assigning a random intercept to each cluster of related subjects. To assess whether there are differences between baseline and at six weeks, we will employ the use of paired t-tests or non-parametric tests for univariable analysis, as appropriate. Additionally, the change in scales over time can be compared between the groups using mixed models approach, wherein an indicator of time (baseline/6 weeks) will define the direction and significance of the change in a model, adjusted independent of other factors.

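### Adjustment of PSS and BRS comparisons is optional and covariates are chosen by observed group differences: the wrong criterion in the randomised arms and an incomplete safeguard in the practitioner contrast

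*Protocol article*

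**What the plan says.** All references are to the protocol article.

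- **Outcomes and timing.** Under Measures (3.4), "PSS is defined as the primary outcome while BRS is the key secondary outcome". Under Data collection (3.3), participants "complete a series of web-based surveys at baseline, six weeks and 12 weeks", so a baseline value of each score is available.
- **Between-group test.** Under Analysis (3.6, Aim 1), "differences between groups will be assessed with a parametric or non-parametric" t-test. No covariate enters this test.
- **Covariate rule.** The same paragraph continues: "Multivariable regression may be utilized to adjust for potential confounders that deem to vary between the groups based on the univariable analysis". It gives no entry threshold for that screen. The general significance rule of the section is "two-sided p-values < 0.05 considered statistically significant".
- **Models.** The paragraph also plans a random intercept for each cluster of friends or matched subjects, and adds that "the change in scales over time can be compared between the groups using mixed models approach". The time indicator of this change model is given as baseline/6 weeks; 12 weeks is not named.
- **Design.** Only the non-meditator controls are randomised (3.5). The practitioners are an observational arm (3.2), matched to controls on age and gender and preferably on neighbourhood (3.1).
- **After data review.** The last paragraph of 3.6 reports a three-group comparison and a Poisson regression to account for confounders, which it does not name.

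**The concern.** The rule asks whether a factor differs between groups, when the relevant questions are whether it predicts the outcome and, in a non-randomised contrast, whether it could confound. The answer to a significance screen depends heavily on sample size, and the final model then depends on the data.

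The two contrasts suffer differently. For Simha Kriya versus placebo, allocation is random, so an imbalance says nothing about which covariates to include. The covariate most likely to help is the baseline value of the same score, and the between-group test leaves it out. The cost is precision on the primary and key secondary outcomes. For practitioners versus controls, confounding is the main threat, and a non-significant screen does not show that it is absent. An estimate may look adjusted while part of the bias remains.

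**Working it through.** The article gives no sample size, effect size, standard deviation or baseline correlation, so there is no planned figure to reproduce. Every input below except the 0.05 level (3.6) is an assumption, shown over a range.

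**1. Randomised arms: what baseline adjustment gains.** Let r be the correlation between baseline and follow-up. Relative to a follow-up t-test (variance 1), the variance factor is 1 − r² with baseline adjustment and 2(1 − r) for a simple change score. The ratio of adjusted to change score is (1 − r²)/[2(1 − r)] = (1 + r)/2. With 1:1 allocation, a 0.5 SD effect and 80% power, n per arm = 2(1.96 + 0.84)² × factor / 0.5², which is 63 at factor 1.

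| r | Adjusted, 1 − r² | Change, 2(1 − r) | Cut against t-test | Cut against change | n per arm, adjusted | Power at 63 per arm, adjusted |
|---|---|---|---|---|---|---|
| 0.3 | 0.91 | 1.4 | 9% | 35% | 58 | 83.7% |
| 0.5 | 0.75 | 1.0 | 25% | 25% | 48 | 90.0% |
| 0.7 | 0.51 | 0.6 | 49% | 15% | 33 | 97.6% |

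The 1 − r² column shows the share of variance left. At r = 0.7 that share is 51% and the cut is 49%. The range of cuts against the t-test is therefore 9 to 49% when computed exactly.

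**2. Practitioner contrast: what a screen misses.** For a confounder with standardised difference g and n per group, a two-sided 0.05 test has expected z = g/√(2/n). The chance of no flag is 1 − [Φ(z − 1.96) + Φ(−z − 1.96)]. For n = 100 and g = 0.2, z = 0.2/0.1414 = 1.414, and the chance is 1 − [Φ(−0.546) + Φ(−3.374)] = 0.707.

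| n per group | g = 0.2 | g = 0.3 |
|---|---|---|
| 50 | 0.83 | 0.68 |
| 100 | 0.71 | 0.44 |
| 200 | 0.48 | 0.15 |

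If the screen were run at 0.20 instead (critical value 1.2816), the figures for n = 100 fall to 0.44 and 0.20.

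**3. What the screen leaves behind.** Simulation with 8,000 runs per setting, one measured confounder correlated 0.5 with the outcome within groups, no true group effect, screen at 0.05. Without adjustment the expected bias is 0.5g, that is 0.10 or 0.15 SD.

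| n, g | Bias (SD): unadjusted / screened / always adjusted | Type I error: unadjusted / screened / always adjusted |
|---|---|---|
| 100, 0.2 | 0.101 / 0.049 / 0.002 | 0.110 / 0.056 / 0.049 |
| 100, 0.3 | 0.150 / 0.039 / 0.001 | 0.190 / 0.062 / 0.052 |
| 200, 0.2 | 0.099 / 0.028 / 0.000 | 0.168 / 0.060 / 0.051 |
| 200, 0.3 | 0.150 / 0.011 / 0.000 | 0.324 / 0.059 / 0.054 |

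The unadjusted test keeps all of the bias, screening removes part of it, and adjusting regardless removes it for a measured confounder.

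**The case against.** Several points on the other side are sound.

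- **The baseline score is not wholly wasted.** A reader might infer that it is, but 3.6 allows a mixed model of change. What remains is that this model is optional, names only baseline and 6 weeks, and gives no baseline-adjusted comparison at 12 weeks.
- **Matching is not ignored.** The cluster random intercept is already planned. It belongs to the models, though, and not to the t-test.
- **Confounding is not certain.** A reader might infer that the practitioner contrast must remain confounded. The article does not support that: age, gender and preferably location are matched, large imbalances would usually be flagged, and the simulated type I error after screening is only 0.056 to 0.062. A confounder-adjusted Poisson regression was also reported, although it was chosen after data review and its covariates are unnamed.
- **The 0.05 screen is inferred.** The article gives no entry threshold; a looser one would miss less.
- **Aim 1 is worded around practitioners versus controls.** So the rule may not have been written with the randomised arms in mind. But the article states no other between-group test of the scales for those arms, and the three-group comparison in the last paragraph of 3.6 brings them in.
- **A covariate list may sit in a separate analysis plan.** That is fair, and the absence of a list is not the point. The point is the selection rule that the article does state.

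**Conclusion.** The point holds as a poorly chosen stated method and should be changed. Adjustment is optional and covariates are selected by observed imbalance. For the randomised arms this is the wrong criterion, and it forgoes a variance reduction of 9% (r = 0.3) to 49% (r = 0.7) against the follow-up t-test, or 35% to 15% against a simple change score. For the practitioner contrast it is a moderate risk: at an assumed 100 per group and a 0.05 screen, a 0.2 to 0.3 SD imbalance is missed 71 to 44% of the time, leaving an average bias of about 0.04 to 0.05 SD in the simulated case. Correlations, group sizes, imbalances and the screening level are all assumed. The direction of the conclusion does not depend on them, but its size does.

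**What to change.** Drop the univariable screen and fix the models by contrast.

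- **Simha Kriya versus placebo:** one prespecified model for PSS and one for BRS, at 6 and 12 weeks, with the baseline value of the same score, age and gender.
- **Practitioners versus controls:** always adjust for age, gender, location and enrolment date, and for other collected factors that precede practice, whatever their p-values. Do not adjust for baseline PSS or BRS, because practice began before baseline and those scores may already carry its effect. The same reasoning applies to COVID-19 history, which may follow practice and is itself an outcome under Aim 3. Use it, and other medical history that may follow practice, only in a sensitivity analysis.
- **Both:** keep the cluster random intercept that 3.6 already plans.
- **Reporting:** since the data have been reviewed, label the revised models as post-review, and state which covariates entered the Poisson regression and why.

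The cost is a few degrees of freedom and some re-analysis. No new data are needed where these factors were recorded.

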### Randomization

3.5

Non-meditators or control arm participants will be randomized into one of the two groups using the REDCap Block Randomization Technique. Participants will be randomized into one of two groups:1)Active Comparator: Participants will be taught the 3 min Simha Kriya practice which involves deep breathing exercises with meditation (twice daily) for the study duration (12 weeks).2)Placebo Comparator: Participants can choose to either read a book of their choice or stay idle for 15 min each day for a total duration of 12 weeks.

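### Aim 1 change analyses stop at 6 weeks in a 12-week study, and the mixed model judges a between-group question by a time indicator instead of a group-by-time term

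*Protocol article*

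**What the plan says.** All references are to the protocol article.

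- **Outcomes (section 3.4, Measures):** "PSS is defined as the primary outcome while BRS is the key secondary outcome".
- **Visits (section 3.3, Data collection):** "Participants will be asked to complete a series of web-based surveys at baseline, six weeks and 12 weeks".
- **Exposure (section 3.5, Randomization):** the active control arm does "deep breathing exercises with meditation (twice daily) for the study duration (12 weeks"; the reading or idle arm also runs for 12 weeks.
- **Aim 1 (section 3.6, Analysis):** the aim is stated for all three visits, and group differences on the scales are assessed with a parametric or non-parametric t-test.
- **Within-group change, Aim 1:** "To assess whether there are differences between baseline and at six weeks, we will employ the use of paired t-tests", or non-parametric tests.
- **Between-group change, Aim 1:** a mixed model can be used to compare change between groups, "wherein an indicator of time (baseline/6 weeks) will define the direction and significance of the change in a model".
- **Aim 2 (section 3.6):** contrasts baseline with 6 weeks and also baseline with 12 weeks, using a mixed model like that of Aim 1.
- **Amendments (section 3.6, last paragraph):** after the 12-week data were reviewed, the three groups were compared separately and Poisson regression replaced linear regression. Nothing is said about the time contrast.

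**The concern.** Both analyses of change in the primary and key secondary outcomes are written for the first 6 of 12 weeks. Change over the full exposure period has no stated analysis, although the data for it are collected.

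The second fault is the term that decides. The model exists to compare change between groups, yet direction and significance are assigned to a time indicator. During a pandemic, stress scores can shift in every group for reasons unrelated to practice, and the Discussion itself gives the changing course of COVID-19 as the reason for repeated comparisons. A significant time coefficient could then be read as a benefit of practice when all groups moved alike. Conversely, a real difference between groups could go unseen. For the two randomised control arms, the time term does not use the contrast that randomisation protects.

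**Working it through.** **1. Time points, side by side (protocol article)**

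| Element | Baseline | 6 weeks | 12 weeks |
|---|---|---|---|
| Surveys (3.3) | yes | yes | yes |
| Randomised activities (3.5) | start | ongoing | end |
| Aim 1 as stated (3.6) | yes | yes | yes |
| Aim 1 paired test of change (3.6) | yes | yes | not named |
| Aim 1 mixed model of change (3.6) | yes | yes | not named |
| Aim 2 contrasts (3.6) | yes | yes | yes |

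The Aim 1 change analyses are the exception. They cover 6/12 = half of the exposure period.

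**2. What the time coefficient estimates**

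Take two groups A and B with mean changes dA and dB from baseline to 6 weeks, in equal numbers.

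- Model with time and group only: the time coefficient estimates (dA + dB)/2, the average change.
- Model with group-by-time, A as reference: the time coefficient estimates dA, the change in A alone.
- The between-group difference in change, dB − dA, is the group-by-time coefficient.

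In neither model is the time coefficient dB − dA. The same holds on the log scale for a Poisson model.

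**3. Illustration of the consequence**

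The article gives no SD, effect size or sample size, so there is no figure of the plan's own to reproduce. All inputs except the test level are assumed: PSS SD 6.5, within-person correlation 0.6, and 50, 100 or 200 per arm in two arms. The level is the article's own: "two-sided p-values < 0.05 considered statistically significant".

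- SD of change = 6.5 × √(2 × (1 − 0.6)) = 5.81.
- With balanced data at two visits, the time test reduces to a one-sample t-test on all change scores. The group-by-time test reduces to a two-sample t-test on change scores.

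Proportion of 8,000 simulated trials with p < 0.05:

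| True changes (A, B) | n per arm | Time term | Group-by-time |
|---|---|---|---|
| −2, −2 (no group difference) | 50 | 0.930 | 0.057 |
| | 100 | 0.998 | 0.049 |
| | 200 | 1.000 | 0.052 |
| −2, +2 (4-point difference) | 50 | 0.037 | 0.929 |
| | 100 | 0.042 | 0.998 |
| | 200 | 0.041 | 1.000 |
| −3, −1 (2-point difference) | 50 | 0.916 | 0.396 |
| | 100 | 0.998 | 0.678 |
| | 200 | 1.000 | 0.928 |

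Hand check at 50 per arm:

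- Equal falls of 2: the standard error of the average change is 5.81/√100 = 0.581, so the ratio is 2/0.581 = 3.44.
- Four-point difference: the standard error is 5.81 × √(2/50) = 1.16, and 4/1.16 is again 3.44 before rounding. An analytic power calculation gives 0.931, in line with the simulated 0.929.

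The third scenario shows the milder case: both arms improve, and the time term looks far more convincing than the evidence for a group difference.

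**The case against.** The case on the other side has real weight.

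- **A reader might infer that the 12-week result is not tested at all.** The article does not support that. Aim 1 sets its group comparison at all three visits, a t-test is named for it, and the Discussion says comparisons were wanted at two later time points. For the randomised arms, a direct comparison at 12 weeks is itself a valid estimate of effect. Only change to 12 weeks lacks an analysis.
- **A reader might infer that the between-group comparison of change has been abandoned.** The same sentence states the intent to compare change between groups. The fault is that the term it names does not deliver that comparison.
- **A reader might infer that repeated scores from one person are treated as independent.** The article describes handling friends and matched subjects "by assigning a random intercept to each cluster of related subjects", but does not say this is the only random effect in the model of change. The covariance structure may be in an analysis plan that is not shown, and the paired tests respect within-person correlation. No error can be established here.
- **The analysis is supplementary and condensed.** It is worded as an additional option, and an article may leave model terms to the analysis plan. That would excuse silence. It does not excuse fixing the time levels at two and naming the wrong term as decisive.

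The 6-week limit may well be a drafting slip, given that Aim 2 includes 12 weeks. The amendments paragraph does not correct it.

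**Conclusion.** The point holds in a limited form. As written, the Aim 1 analyses of change in PSS and BRS omit weeks 6 to 12, at odds with the article's own visits, exposure period, Aim 1 statement and Aim 2 contrasts. The mixed model also assigns the between-group question to a term that cannot answer it. Followed literally, that rule would call a change shared by all groups significant and could miss a true group difference.

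The algebra needs no assumed values. The size does: the rejection rates of 0.93 to 1.00 with no group difference, and about 0.04 with opposite changes, rest on the assumed SD, correlation, sample sizes and changes, and only show how far the two tests can diverge. If the analysis plan that is not shown already specifies group-by-time terms at both follow-up visits, the remedy is to correct the article's wording to match.

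**What to change.** 1. Fit the Aim 1 mixed model with time as a three-level factor (baseline, 6 and 12 weeks), group, and group-by-time, on the scale of the regression finally used.
2. Judge the between-group comparison of change by the group-by-time contrasts at 6 and 12 weeks. Include the randomised Simha Kriya versus reading/idle contrast among them.
3. State that the model accounts for repeated scores within a participant as well as for the matched cluster.
4. Report within-group paired tests descriptively, at both follow-up visits.
5. Because Aim 2 borrows the Aim 1 model, carry the corrected wording over to it.
6. Disclose the revision as made after the 12-week data had been reviewed.

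This error does not require a new primary time point, nor does it require making the randomised contrast primary. Either would be a further choice made after seeing the data.

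The cost is revised wording and one refitted model per scale on data already collected. It needs no new participants or visits. The price is that the contrasts carry a post-data label.

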Aim 2 Analysis. To Compare Protection and Recovery from COVID 19 infection between seasoned Isha yoga practitioners and controls as demonstrated by:a.Self-reported duration of fever and respiratory symptoms in COVID-19 positive participantsb.Self-reported readiness to return to work (or a feeling of being physically and mentally fit)

We will calculate the protection and recovery rates from COVID-19 infection as defined by the aforementioned criteria. Given the continuous nature of the criteria used to assess symptom duration and sense of recovery, differences between groups will be assessed in a univariable manner with a parametric or non-parametric *t*-test. We will perform spot analysis at the three defined points to capture the point prevalence of recovery rates. We also intend to assess the differences between the prevention and recovery rates at baseline and six weeks and baseline and twelve weeks. We will employ the mixed model technique similarly to the analysis suggested in the aim #1 analysis.

Analysis of Aim 3: To compare Prevalence rates of diagnosed COVID-19 infection between the seasoned Isha yoga practitioners and age and gender matched controls at baseline, 6 weeks, and 12 weeks.

We will compute period prevalence of diagnosed COVID-19 infections as a measure of frequency. Since the data to be analyzed are not dependent on duration, we intend to compute the prevalence rates at the following time points: baseline, 6 weeks, and 12 weeks. The result would be reported as the portion of study population with COVID-19 at the specified time point.

Finally, we will perform an exploratory analysis of the data collected by comparing the effect of yoga practices and their duration between the 3 study groups to estimate a dose-response trend if possible.

Compliance is defined as 3 days of activity each week for at least 3 weeks from baseline to 6 weeks, or a minimum of 6 weeks from baseline to 12 weeks. Measures of frequency and association will also be calculated. We will complete exploratory analysis by comparing the different yoga practices and their duration between the 3 study groups to assess a dose-response pattern.

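### The Aim 1 mixed model is meant to compare change between groups, but the term named as deciding significance is time, not group-by-time

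*Protocol article*

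**What the plan says.** All of this stands in the Analysis section (3.6) of the protocol article. For Aim 1, with PSS as primary and BRS as key secondary outcome, it lists three kinds of analysis.

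- **Between groups:** "differences between groups will be assessed with a parametric or non-parametric *t*-test", with optional regression adjustment and a mixed model that handles friends and matched subjects "by assigning a random intercept to each cluster of related subjects".
- **Before and after:** "To assess whether there are differences between baseline and at six weeks, we will employ the use of paired t-tests or non-parametric tests". The text does not say whether these tests are run within each arm or on everyone together.
- **Change between groups:** as an additional analysis, "the change in scales over time can be compared between the groups using mixed models approach". The same sentence goes on to say how that model will be read: "an indicator of time (baseline/6 weeks) will define the direction and significance of the change in a model".

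The significance rule is "two-sided p-values < 0.05 considered statistically significant". The Aim 2 text adds: "We will employ the mixed model technique similarly to the analysis suggested in the aim #1 analysis". A closing paragraph of the section reports later changes, namely a comparison of three groups and Poisson regression. No part of the article names a group-by-time term or another between-group contrast of change.

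**The concern.** The sentence on the change model sets a between-group aim and then gives the decision to a term with no between-group contrast in it. Without an interaction in the model, the time coefficient is the change averaged over the groups. With an interaction and reference coding, it is the change in the reference group alone. Neither answers whether Simha Kriya changed stress more than reading or sitting idle did.

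This matters for the trial's stated purpose. The Discussion wants the randomised comparison to show that taking up a yoga practice improves mental health in non-meditators. It also justifies the repeat visits by the changing course of the pandemic. A shared movement in stress over six weeks is therefore plausible, though the article does not say that PSS moved. The concurrent placebo arm is there to remove such a movement, and a criterion that looks only at time does not use it. The random intercept for friend clusters does not remove a common time trend either.

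**Working it through.** The article states no sample size, SD, correlation or expected change, so there is no figure of its own to reproduce. What follows illustrates the literal rule.

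**Inputs from the article:** two-sided 5% level; baseline and 6 weeks as the two levels of the time indicator; two randomised control arms.

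**Inputs assumed:** PSS SD 7; correlation between baseline and 6 weeks r = 0.6; 100 per randomised arm; both arms fall by 1.5 points for reasons unrelated to practice. Clustering of friends is ignored, and PSS is treated as continuous.

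**Step 1, SD of change.** 7 × √(2 × (1 − 0.6)) = 6.26.

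**Step 2, time coefficient pooled over 200 people.** SE = 6.26/√200 = 0.443; z = 1.5/0.443 = 3.39; P(significant) ≈ Φ(3.39 − 1.96) = 0.92.

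**Step 3, time coefficient read as change in one reference arm of 100.** SE = 6.26/√100 = 0.626; z = 1.5/0.626 = 2.40; P(significant) ≈ 0.67.

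**Step 4, group-by-time.** The true difference in change is 1.5 − 1.5 = 0, with SE 6.26 × √(2/100) = 0.885. It rejects in 5% of trials, whatever the common fall.

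**Range of the pooled time term:**

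| Assumption varied | P(time term significant) |
|---|---|
| Base case | 92% |
| r = 0.5 (SD of change 7.00, SE 0.495, z 3.03) | 86% |
| r = 0.7 (SD of change 5.42, SE 0.383, z 3.91) | 97% |
| 50 per arm, fall of 1 point (SE 0.626, z 1.60) | 36% |
| 200 per arm, fall of 2 points (SE 0.313, z 6.39) | about 100% |
| No common fall | 5% |

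The result also depends on the random effects. Suppose the model has only the cluster intercept, with no person-level term, and that intercept absorbs nothing. The model then uses SE = √(2 × 49/200) = 0.70, and significance needs a change above 1.96 × 0.70 = 1.37. The chance is Φ((1.5 − 1.37)/0.443) ≈ 61%, still far above 5%.

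**Check with three arms.** With three equal arms, r = 0.5 and a common shift of 0.2 SD, the time main effect is significant in 69% of trials at 50 per arm and 93% at 100 per arm. In 20,000 simulated trials at each of three settings, the between-arm tests of change rejected in 4.9% to 5.3%.

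**The reverse case.** If the active arm falls 2 points and an equal placebo arm rises 2, the expected time coefficient is (−2 + 2)/2 = 0, although the arms differ by 4 points.

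**The case against.** The strongest reply is that the sentence opens with a between-group comparison of change, so the time indicator may only be loose wording for how time enters that model. The analysis is also additional and optional, exact model terms often sit in an analysis plan, and an article condenses. Part of this stands: the text shows a mismatch between aim and criterion, not a declared choice against an interaction. It does not remove the point, because the article did not leave the deciding term open. It named one, and that one gives the wrong answer if followed.

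Several stronger readings are tempting, and the documents do not support them.

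- **A shared trend will be reported as a yoga effect.** It could be, if the sentence is applied literally. Aim 1 also has between-group t-tests, and the section reports a three-group comparison; a common trend biases neither.
- **Opposite effects in the two arms would go undetected.** Only the time coefficient misses them. In the reverse case, with equal baselines, SD 7 and 100 per arm, a follow-up t-test of active against placebo has SE 7 × √(2/100) = 0.99, z = 4/0.99 = 4.04 and power of about 98%.
- **The paired tests are misused.** The article uses them to ask whether scores differ between baseline and six weeks, which a paired test does answer. It does not say they are run per arm or count as evidence of benefit. Run per arm in the base case, exactly one arm would be significant in 2 × 0.669 × 0.331 = 44% of trials, but that figure depends on a use the article never proposes.
- **Regression to the mean adds to the drift.** Table 1 has no stress threshold for entry, so no group-level regression to the mean is expected.
- **Aim 2 takes over the same faulty model.** The text says only that the technique is used similarly, which could mean just the cluster random intercept.

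**Conclusion.** The point holds as a wording fault with a real consequence. The change analysis names the time indicator as the term that defines direction and significance, and that term cannot show whether change differs by group. The between-group t-tests do not repair this, since they are not said to compare change and Aim 1 frames the comparison as seasoned practitioners against controls.

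Under the assumed inputs, a common fall of 1.5 points makes the time term significant in about 92% of trials with no yoga effect, against 5% for group-by-time. For 50 to 200 per arm and falls of 1 to 2 points, the range is 36% to about 100%. These figures rest wholly on the assumed SD, correlation, arm size and trend; with no trend, both tests reject in 5%. Because the model is optional and stands beside unbiased between-group tests, this is a correction to make to the text and does not show that the trial's conclusions are unsound.

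**What to change.** Rewrite the sentence on the change model so that:

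- the model has terms for group, visit and group-by-visit, with visit covering baseline, 6 and 12 weeks (Aim 1 lists week 12, but the time indicator leaves it out);
- the test of change is the group-by-visit contrast with its confidence interval, in particular Simha Kriya minus placebo, which is the randomised comparison;
- the time coefficient and any paired before-and-after results are descriptive, and their p-values are not used as evidence of benefit;
- the same rule applies in Aim 2 wherever a model of change is used, and under the Poisson regression adopted later.

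The cost is one sentence and one extra model term. No new data are needed. The article indicates that the 12-week data have already been reviewed, so the contrast can be obtained by re-analysis.
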